### Non-inclusion criteria

2.4.

Patients will not be included if (i) birth weight is less than 2 kilos and/or gestational age less than 37 weeks (ii) if they have a CCHD not requiring cardiac surgery with CBP during the first 2 months of life And (iii) if they have a proven chromosomal abnormality or genetic syndrome associated with their CCHD.

### Procedure overview

2.5.

Each recruited patient will participate in the study for 24 months (Figure 1). Following the recruitment (visit 0, V0) conducted in the neonatal period before cardiac surgery, a preoperative brain MRI will be performed before surgery (visit 1, V1) if the health of the neonate allows for this. During the 15 days following the surgery, a postoperative brain MRI is performed (visit 2, V2). Visits 1 and 2 aim to assess preoperative brain injuries and those that appear or worsen postoperatively. The preoperative MRI should not delay cardiac surgery. Visits 3 (V3), 4 (V4), and 5 (V5) will involve neurodevelopmental assessments at 4 months, 12 months, and 24 months, respectively, conducted by a single child neurologist ([name]) and the Alberta Infant Motor Scale (AIMS) assessment at 4 months and 12 months. These assessments will be scheduled and conducted during conventional follow-up cardio-pediatric appointments. During visit 5 (V5), at 24 months, a standardized neuropsychological assessment will be performed using the Bayley-IV test.

**Figure 1 F1:**
[figure not shown]
24-month monitoring of patients born with CCHD operated on within the first 2 months of life. CPB, Cardiopulmonary bypass; CHD, Congenital Heart Disease; MRI, Magnetic Resonance Imaging; AIMS, Alberta Infant Motor scale; BAYLEY scale fourth edition.

#### Prenatal period

2.5.1.

The La Timone Enfants University Hospital (Marseille) is the regional reference center for pediatric cardiac surgery in the Provence Alpes Côtes d'Azur (PACA) region, south-east of France. As part of pregnancy monitoring, and in the event of abnormal cardiac measurements, parents are referred to an ultrasound physician specializing in fetal cardiac ultrasounds. When the parents decide to continue the pregnancy, they meet the cardiac surgeon, who explains the details of the operation to be performed after birth and present the study to the parents to explain the objectives, constraints, and procedures.

#### Post-partum period

2.5.2.

After birth, which takes place in a level 3 maternity ward, patients are admitted to the Pediatric Intensive Care Unit (PICU) at La Timone Enfants Hospital for clinical stabilization, cardiac assessment, and emergency procedures. If the parents or legal representatives were informed of this study in advance and agreed to participate, they would be asked to sign the consent form with the child neurologist. In the unlikely event that the parents could not be informed prior to the beginning of the study, and where the study's procedures would be compatible with treatment within the framework of the patient's care, consent will be obtained upon the child's admission to the PICU but after a 24-hour reflection period.

### Brain MRI

2.6.

A pre- and postoperative brain MRI will be performed on a clinical 3 T Vida MRI system (Siemens Medical Systems) using a 64-channel head coil. Protocol will include 2D T1-weighted, T2-weighted, and diffusion-weighted imaging and 3D isotropic T1-weighted imaging to highlight preoperative brain injuries, as well as those that appear or worsen postoperatively. All MRI sequences use thin cuts (1 mm), and the entire MRI protocol is adapted for neonates and infants to optimize contrast. The preoperative brain MRI will be performed just prior to surgery and the postoperative one within 15 days following cardiac surgery.

The neonate will be comfortably secured in an adapted cocoon after administration of a normal food ration, without general anesthesia or injection of a contrast product. The completion time for the MRI is between 30 and 45 min.

### Genetic workup

2.7.

A biobank called SEA-CARREG has been established by the cardiology department, and all recruited patients will have a genome.

#### AIMS - Alberta infant motor scale

2.8.1.

The AIMS assessment will be performed at 4 months and 12 months. The AIMS is a standardized tool allowing the neuromotor assessment of infants from 0 to 18 months old and the identification of children with abnormal motor development. The scale consists of 58 items exploring the functional motor skills of infants in sitting, standing, prone, and supine positions. The interpretation of the results for each position and the overall score will be completed using percentile ranks according to the age of the infant. These assessments will be scheduled and performed during conventional cardio-pediatric follow-up visits.

#### Bayley-IV

2.8.2.

A standardized neuropsychological assessment using a Bayley-IV test will be performed at 24 months. The Bayley-IV test is used to assess children aged 1 to 42 months. This is a standardized scale (mean = 100, standard deviation = 15), which has demonstrated good sensitivity in detecting neurodevelopmental disorders in patients with CCHD. The items are organized according to the level of difficulty. The scale contains five subscales, three of which (cognition, motor skills, language) require interaction with the child and will be used for the analysis. The two other subscales will beassessed through questionnaires completed by the parents or legal representatives and relate to the socio-emotional sphere, communication of needs, and self-regulation for the first part and adaptive behavior, communication, and autonomy for the second part. These results will not be retained for analysis. This assessment will be scheduled and performed during a conventional cardio-pediatric follow-up visit.

### Morbidities

2.9.

An analysis will be conducted for postoperative morbidities (see Table 2), including cardiac, hemodynamic, surgical, infectious, and neurological morbidities. Each of these complications will be analyzed independently.

Perioperative demographic and clinical data, including postoperative complications, will be collected retrospectively from prospectively completed medical files. We are particularly interested in the following data:
(i)demographic, including gender, education level, and economic status of the parents;(ii)preoperative, including whether there was a prenatal diagnosis of complex CHD, gestational age at birth, birth weight, head circumference at birth, Apgar score at 5 min, type of complex CHD, whether a Rashkind procedure was performed, the type of ventilation and its duration in days, hypotension requiring treatment, cardiac arrest, and arrhythmia.(iii)intraoperative, including age and weight at the time of surgery, hematocrit in the operating room, type of surgery, CPB time in minutes, selective cerebral perfusion time, and circulatory arrest time in deep hypothermia in minutes.(iv)postoperative, including ventilation (non-invasive, mechanical), duration in days, anesthesia, sedatives and exposure to antiepileptics, medication names and number of days used, and total and postoperative length of their stay in days.

## Statistical analysis

3.

### Analytical strategy

3.1.

The data analysis will be performed blindly using R -3.4.1 for Windows.

#### Sample size

3.1.1.

Two previously published studies that reported a significant correlation between age at surgery and the incidence of WMIs included 26 and 37 patients, respectively (7, 8). Based on the active file of patients with complex CHD operated on each year in Cardiac Surgery at the La Timone Enfants Hospital, the total number of subjects included will be 100. With this number of 100 included patients and according to the values of (i) a 5% bilateral alpha risk and (ii) 80% statistical power, we estimate the minimum correlation coefficient between age at surgery and Bayley-IV test scores as 0.39.

According to the same hypotheses (5% bilateral alpha risk and 80% statistical power), and based on the intended number of patients recruited for each (Clancy) CHD subtypes, the minimum correlation coefficient that could be highlighted between age at surgery and Bayley-IV test scores is:
*r* = 0.38 for class I, two-ventricle heart without arch obstruction (*n* = 50)*r *= 0.65 for class II, two-ventricle heart with arch obstruction (*n* = 15)*r* = 0.76 for class III, single ventricle heart without arch obstruction (*n* = 10)*r* = 0.53 for class IV, single ventricle heart with arch obstruction (*n* = 25)”

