#### Main analysis

3.1.2.

The analysis of the main objective will be based on the evaluation of the correlation between the age at surgery (in number of days of life) and the main analysis criteria selected, namely the neurodevelopmental outcomes at 24 months assessed using the scores obtained on the Bayley-IV scale. The analysis will be conducted for the entire cohort and separately for each type of complex CHD to define the optimal age for surgery for each complex CHD type. To do this, Pearson's correlation coefficient will be estimated with a 95% confidence interval if the application conditions are met (otherwise, the non-parametric Spearman's rank correlation coefficient will be estimated with a confidence interval of 95%). A ROC curve will be plotted to curve to determine (according to Youden's method) the optimal threshold for the age at surgery that discriminates delayed neurodevelopment / normal neurodevelopment according to the main criterion, i.e. neurodevelopment at 24 months according to the Bayley-IV scale. The first secondary endpoint based on the AIMS scores at 4 months and 12 months will be analyzed using the same previously described strategy. The next secondary endpoint based on the clinical assessment by the child neurologist (neurodevelopment considered normal vs. abnormal) at 4 months, 12 months, and 24 months will be analyzed using a comparison test for quantitative data. A Student's t-test will be used if the application conditions are met; otherwise, the non-parametric Mann-Whitney test will be used.

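### The minimum detectable correlation of 0.39 stated for 100 infants is wrong: the stated inputs give about 0.28, and 0.39 belongs to about 48 to 50 infants

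*Protocol article*

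**What the plan says.** The Sample size section (3.1.1) takes the number of infants from the centre's active patient file and then reports what that number can detect. It starts from "With this number of 100 included patients", adds "a 5% bilateral alpha risk" and "80% statistical power", and concludes: "we estimate the minimum correlation coefficient between age at surgery and Bayley-IV test scores as 0.39".

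The next paragraph repeats the exercise for the four anatomical classes at unchanged alpha and power: "According to the same hypotheses (5% bilateral alpha risk and 80% statistical power". The first entry is "0.38 for class I, two-ventricle heart without arch obstruction", with n = 50. The others are 0.65 for class II (n = 15), 0.76 for class III (n = 10) and 0.53 for class IV (n = 25).

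The Main analysis section (3.1.2) names the statistic to which these figures refer: "Pearson's correlation coefficient will be estimated with a 95% confidence interval if the application conditions are met". Spearman's coefficient is the fallback. The section states that the analysis is done for the entire cohort and separately by type of heart disease.

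**The concern.** At fixed alpha and power, the smallest detectable correlation must fall as the number of infants rises. The section gives 0.39 for 100 infants and 0.38 for 50, so at least one of the two cannot be right.

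The whole-cohort figure describes the sensitivity of the main correlation analysis. Taken at face value, it says that correlations between about 0.28 and 0.39 lie below the study's reach, although the power there runs from about 80% to 98%. In terms of explained variance, 0.39 is 0.39² = 15.2%, while 0.276 is 0.276² = 7.6%. The article therefore claims that an association must be about twice as strong, on that scale, as the design requires.

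**Working it through.** **Inputs, all from the Sample size section:** n = 100; two-sided alpha 0.05 (z = 1.960); power 0.80 (z = 0.8416); class sizes 50, 15, 10 and 25. The statistic, Pearson's r, is from the Main analysis section. The null hypothesis is a correlation of zero.

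**Step 1. Try to reproduce 0.39 at n = 100.** By Fisher's z,

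r = tanh[(1.960 + 0.8416) / √(n − 3)] = tanh(2.8016 / √97) = tanh(0.2845) = 0.277.

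Other methods agree:
- exact power under a bivariate normal distribution: 0.276
- t-based critical value with bias-corrected Fisher z: 0.276
- noncentral t with fixed ages: 0.272
- Spearman, with the usual variance inflations: 0.282 to 0.285
- one-sided test by Fisher's z: 0.247

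None of these comes near 0.39.

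**Step 2. Find the n to which 0.39 belongs.** Inverting Fisher's z with atanh(0.39) = 0.4118,

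n = (2.8016 / 0.4118)² + 3 = 49.3, rounded up to 50.

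The t-based version gives 48.5, rounded up to 49. By the exact method, 48 infants detect 0.391 and 49 detect 0.387. So 0.39 is the value for about 48 to 50 infants.

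**Step 3. Power at r = 0.39 with n = 100.** By Fisher's z, 0.4118 × √97 − 1.960 = 2.096, and the normal probability below 2.096 is 0.982. The exact calculation gives 0.983. The power is thus about 98%, against the stated 80%.

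**Step 4. Check the class values with the same methods.**

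| Group | n | Stated | Exact | t-based | Fisher z |
|---|---|---|---|---|---|
| Class I | 50 | 0.38 | 0.384 | 0.384 | 0.387 |
| Class II | 15 | 0.65 | 0.653 | 0.657 | 0.669 |
| Class III | 10 | 0.76 | 0.761 | 0.770 | 0.785 |
| Class IV | 25 | 0.53 | 0.526 | 0.528 | 0.535 |
| Whole cohort | 100 | 0.39 | 0.276 | 0.276 | 0.277 |

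To two decimals, the exact method returns all four class values as printed. The approximations drift upwards in the smallest classes. Only the whole-cohort row fails, by 0.39 − 0.276 = 0.114.

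**Step 5. Look for unstated inputs that would rescue 0.39.** Keeping n = 100 and 80% power would need a two-sided alpha of about 0.0013. An alpha of 0.05/3 with 95% power gives 0.387 to 0.389. Both contradict the stated 5% and 80%. Attrition would have to leave about half of the 100 infants evaluable. The section states no such loss.

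**The case against.** The strongest reply is that the error does no harm. It is conservative: 100 infants are ample for a correlation of 0.39. The number 100 comes from the centre's patient file, so 0.39 is an output of the sample size and not the reason for it. The correlation will be reported with a 95% confidence interval, so a null result can be read from the interval. All of this stands. It limits the consequences but does not make the figure correct.

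Three stronger readings are tempting, and the documents do not support them.

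- *The class values are wrong too.* Fisher's z suggests slightly higher values for classes II and III (0.669 and 0.785). That reflects the approximation at n = 15 and n = 10; the exact method confirms the printed 0.65 and 0.76.
- *The figures ignore losses before 24 months.* The article gives no loss rate, and its Recruitment section describes the 100 infants as receiving both MRIs and the 24-month Bayley-IV. A condensed article may leave an attrition allowance to the full protocol. Any adjusted value would rest on an assumed rate.
- *The study's size is unjustified, or a later study will be mis-sized.* The size rests on feasibility, and nothing says that the later interventional study would be planned from 0.39.

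**Conclusion.** The concern holds for one number. On the stated inputs, the minimum detectable correlation for 100 infants is about 0.28, and the stated 0.39 is about 40% too high (0.39 / 0.276 = 1.41). The conclusion does not depend on the choice of method, since every two-sided calculation, including those for Spearman, lies between 0.272 and 0.285. The conflict with 0.38 at n = 50 is visible in the text without any calculation.

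The result assumes a test of zero correlation and 100 infants contributing both an age at surgery and a Bayley-IV score. The text does not show how 0.39 arose. A value computed for about 50 infants and not updated would fit, but this cannot be confirmed. The error understates the sensitivity of the whole-cohort analysis and affects no endpoint, analysis or recruitment target.

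**What to change.** In the Sample size section, replace 0.39 with 0.28 for the whole cohort of 100. If 0.39 was meant for a smaller evaluable number, state that number and the reason for it; it would have to be about 48 to 50 infants. Leave the four class values unchanged. It would help to name the calculation method so that all five figures can be reproduced. The cost is one corrected sentence, with no change to recruitment, data collection or analysis.

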#### Main analysis

3.1.2.

The analysis of the main objective will be based on the evaluation of the correlation between the age at surgery (in number of days of life) and the main analysis criteria selected, namely the neurodevelopmental outcomes at 24 months assessed using the scores obtained on the Bayley-IV scale. The analysis will be conducted for the entire cohort and separately for each type of complex CHD to define the optimal age for surgery for each complex CHD type. To do this, Pearson's correlation coefficient will be estimated with a 95% confidence interval if the application conditions are met (otherwise, the non-parametric Spearman's rank correlation coefficient will be estimated with a confidence interval of 95%). A ROC curve will be plotted to curve to determine (according to Youden's method) the optimal threshold for the age at surgery that discriminates delayed neurodevelopment / normal neurodevelopment according to the main criterion, i.e. neurodevelopment at 24 months according to the Bayley-IV scale. The first secondary endpoint based on the AIMS scores at 4 months and 12 months will be analyzed using the same previously described strategy. The next secondary endpoint based on the clinical assessment by the child neurologist (neurodevelopment considered normal vs. abnormal) at 4 months, 12 months, and 24 months will be analyzed using a comparison test for quantitative data. A Student's t-test will be used if the application conditions are met; otherwise, the non-parametric Mann-Whitney test will be used.

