For patients with TGA (Transposition of Great Arteries) or HLHS (Hypoplastic Left Heart Syndrome), later cardiac surgery leads to a higher incidence of white matter injuries (WMI) (7, 8), which is a well-known prognostic factor for motor (9–12), language (11), and cognitive (10, 12, 13) impairment, as well as behavioral issues (14). Additionally, Anderson et al. (15) demonstrated that conducting the arterial switch operation (ASO) on neonates with TGA before the third day of life reduced the major postoperative morbidity of these patients in terms of neurological (occurrence of seizures, ischemic stroke), cardiological, and infection complications. Patients with left ventricle hypoplasia operated on later in the neonatal period also presented higher postoperative morbidity (16). Similarly, patients with TGA given the ASO after 2 weeks of life experienced impaired perioperative brain growth and slowed language development (17). Conversely, a major hypotrophy (weight < third percentile) or hemodynamic instability can delay the surgery, which may then be considered too risky. The fetal, pre and intraoperative risk factors of brain injuries are listed in the Table 1. All postoperative morbidities (Table 2) are deemed as potential risk factors for brain injuries.

**Table 1 T1:** Foetal and preoperative risk factors of brain injuries.

	Foetal period	Preoperative period	Intraoperative period
Risk Factors of Brain injuries	Gestational Age	Postnatal diagnosis	CPB duration (min)
	IUGR	Lower arterial oxygen saturation	Aortic clamp time (min)
	Brain volume	Lower apgar scores at 5 min	DHCA (min)
			Selective cerebral perfusion (min)
	Brain immaturity	Abnormal aEEG background pattern	Low Flow
		Longer time to surgery	
		Brain lactates	
		Low flow	
		Male sex	

CPB, Cardiopulmonary bypass; DHCA, Deep hypothermia with circulatory arrest; IUGR, Intrauterine growth restriction; aEEG, amplitude EEG.

**Table 2 T2:** Classification of post-op morbidities.

Morbidity category	Morbidities	
Cardiac / Respiratory	• Cardiac arrest, arrhythmias, JET • Low cardiac output syndrom • Extracorporeal membrane oxygenation • Post-op high-output failure • Re-intubation for acute respiratory distress	• Neonatal necrotizing enterocolitis • Systemic vein thrombosis • Acute renal deficiency with dialysis • Delayed sternal closure • Length of intensive care unit stay
Infectious	• Septicemia, fungemia • Infection of the surgical site, mediastinitis • Endocarditis	• Meningitis • Pneumonia

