Neurological	• Ischemic cerebrovascular accident • Hemorrhagic cerebrovascular accident	• Epileptic seizure • Cerebral thrombophlebitis
Surgical	• Recurring diaphragmatic paralysis/paresis • Definitive AV block with device • Acute hemorrhaging requiring revision surgery	• Cardiac tamponade • Unplanned revision surgery • Chylothorax

There is no consensus regarding the optimal age for surgery in terms of morbidity and neurodevelopmental outcomes, and its definition is a real challenge. Importantly, at the present time, there are no established rules for determining the timing of surgery in our department. For the most common CHD types, the TGA are corrected during the first ten days of life. There is a more pronounced degree of variation for HLHS. This common practice won't be changed for our observational study.

Our aim is to determine the relationship between surgical timing and long-term neurodevelopmental outcomes for various types of complex CHD. Similarly to Anderson et al. (15) with postoperative morbidity, we aim to determine a cut-off point for surgical timing that will improve neurodevelopmental outcomes. For each type of CHD, we aim to determine a cut-off for surgical timing based on postoperative morbidity and neurodevelopmental outcomes. We hope that our findings will contribute to the development of surgical timing guidelines in the future.

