### Inclusion criteria

2.2.

In this study, we will recruit infants aged 2 months or less with complex CHD requiring surgery with extracorporeal circulation during their first 2 months of life at the La Timone Enfants Hospital in Marseille. The included patients should be born full-term (at more than 37 weeks). The eligible complex CHDs correspond to the anatomical classification of Clancy et al. (19), (Table 3).

**Table 3 T3:** Classification of complex congenital heart diseases selected for the study, according to Clancy *et al*. (19).

Classification Number	Anatomic Classification (10)	Complex CHD
I	Two-ventricle heart without arch obstruction	TGA with intact ventricular septum
		TGA/VSD
		Tetralogy of Fallot/PA
		Truncus Arteriosus
		TAPVR
II	Two-ventricle heart with arch obstruction	TGA/VSD/CoAo
		VSD/CoAo
		VSD/Interrupted aortic arch
III	Single-ventricle heart without arch obstruction	Unbalanced AVCD
		Tricuspid atresia
		Mitral atresia
		Heterotaxy
		Double-outlet left ventricle
		Double-outlet right ventricle
		Single ventricle (other)
IV	Single-ventricle heart with arch obstruction	HLHS

PA, Pulmonary Atresia; AVCD, Atrioventricular Canal Defect; VSD, Ventricular Septal Defect; CoAo, Coarctation of the Aorta; HLHS, Hypoplasia of Left Heart Syndrome; TAPVR, Total Anomalous Pulmonary Venous Return; TGA, Transposition of the Great Arteries.

For all patients, we must obtain informed consent from both parents (except in special cases justifying consent from just one parent) or from legal representative(s). The parents or legal representatives must be able to read and speak French. Additionally, the included patients will need to be affiliated with French social security.

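### Age at surgery, counted from birth and used unadjusted, combines age at admission with the wait for surgery, so the main correlation and cut-off can partly reflect late diagnosis

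*Protocol article*

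**What the plan says.** Section 3.1.2 (Main analysis) rests on the "evaluation of the correlation between the age at surgery (in number of days of life) and the main analysis criteria selected". The method is a simple correlation: "Pearson's correlation coefficient will be estimated with a 95% confidence interval if the application conditions are met", with Spearman's coefficient as the fallback. A ROC curve with Youden's method then gives "the optimal threshold for the age at surgery that discriminates delayed neurodevelopment / normal neurodevelopment according to the main criterion". Neither step has a covariate.

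Eligibility does not depend on when the heart defect was found. Section 2.2 states that "we will recruit infants aged 2 months or less with complex CHD", and section 2.4 does not bar infants diagnosed after birth. Section 2.5.2 gives a consent route at intensive care admission for families who were not informed beforehand, and calls that situation unlikely. Section 2.9 records whether there was a prenatal diagnosis, and also "total and postoperative length of their stay in days". Age or date of admission is not in its list.

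Table 1 has "Postnatal diagnosis" and "Longer time to surgery" as separate preoperative risk factors for brain injury. Section 3.1.3.4 plans secondary multivariable models that keep age at surgery as the explanatory variable of interest and add prognostic factors chosen in advance from the literature.

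On use of the results, the Introduction says: "We hope that our findings will contribute to the development of surgical timing guidelines in the future".

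**The concern.** A surgical-timing guideline can act on the days between admission and surgery. It cannot act on the days before a late-diagnosed infant reaches the unit. Age in days of life adds the two together. If late diagnosis does harm of its own, as Table 1 suggests, late-diagnosed infants will tend to have both a higher age at surgery and a lower Bayley-IV score. That alone produces a negative correlation, even if the wait in hospital has no effect.

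The Youden cut-off inherits the problem. It is also hard to apply to an infant admitted close to the cut-off or beyond it. The same exposure is used for the AIMS scores, the clinical assessment, white matter injury, morbidity and length of stay. At stake is whether a negative correlation can be read as support for choosing an earlier surgical date.

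**Working it through.** **Inputs from the article.** n = 100, two-sided 5% level, exposure counted from birth, Bayley-IV SD 15. The article gives no figure on this point: no late-diagnosed share, no age at admission, no spread of waits. Everything else below is an assumption.

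**Identity.** Age at surgery T = A + W, with A the age at admission and W the days from admission to surgery. For an infant admitted at birth, A = 0 and T = W.

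**Scale.** The smallest correlation detectable with 80% power at n = 100 is tanh((1.960 + 0.842)/√97) = 0.277. Section 3.1.1 states 0.39, which does not reproduce. That is a separate matter and nothing here depends on it.

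**Closed form.** Let W have no effect on the score and SD s. A share q is diagnosed late, which adds D days to age and lowers the score by h SD. Then

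corr(T, score) = −q(1−q)Dh / √[(s² + q(1−q)D²)(1 + q(1−q)h²)],

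and the chance of significance is about Φ(|atanh r|√97 − 1.96) + Φ(−|atanh r|√97 − 1.96).

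| q | D (days) | h (SD) | s (days) | r | Chance of significance |
|---|---|---|---|---|---|
| 5% | 5 | 0.33 | 10 | −0.078/√(101.19 × 1.005) = −0.01 | 5% |
| 20% | 10 | 0.67 | 4 | −1.072/√(32.0 × 1.072) = −0.18 | 45% |
| 40% | 10 | 1.0 | 4 | −2.40/√(40.0 × 1.24) = −0.34 | 94% |

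The last row is deliberately extreme: 40% diagnosed late and a 15-point loss.

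**Simulation.** Wait mean 9 days and SD 6, with no effect on the score; residual SD 15. Late diagnosis costs 5 points, with or without a further 0.5 points per day before admission. Delay before admission is exponential. Entries are for 10, 25 and 40% diagnosed late.

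| Setting | Mean r, total age | Significant, total age |
|---|---|---|
| Mean delay 10 days, per-day harm | −0.12, −0.22, −0.27 | 25, 59, 77% |
| Mean delay 5 days, per-day harm | −0.05, −0.10, −0.13 | 8, 18, 25% |
| No per-day harm | −0.02 to −0.08 | 5 to 12% |

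With 5% diagnosed late, the rate is 5 to 13% across these settings. In the first row, a wait SD of 4 days gives 32 to 86%, and an SD of 9 days gives 17 to 60%.

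**What adjustment does.**
- Total age plus a yes/no term for late diagnosis: in the first row the rates fall to 8, 19 and 32%. With a 5-day mean delay they are 6 to 8%, and with no per-day harm about 5%.
- Wait and age at admission as separate terms: the wait term is significant in about 5% of studies in every setting, and adding the diagnosis term leaves it there.

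**The case against.** The strongest reply is that counting from birth is deliberate. The Introduction treats the whole preoperative period as one of hypoxia and instability, and the main objective asks about age at surgery in days of life. An undiagnosed infant is also unrepaired, so those days belong to the exposure under study. This stands, and it is why age at surgery should remain the primary exposure.

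Second, within the simulation the highest rates need 25 to 40% late-diagnosed, a 10-day mean delay, and harm per day before admission but none per day after it. Nothing in the article supports that asymmetry. Section 2.5.2 also suggests that few families arrive uninformed, though it gives no figure and is not a count of postnatal diagnoses. This stands as a limit on the size of the problem.

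Third, prenatal diagnosis is collected and adjusted models are planned. That removes most of the distortion in the mild settings. It does not reach the main correlation or the cut-off, and a yes/no term leaves the days before admission inside the exposure. That the article does not list the covariates is no fault, since such a list commonly sits in the full protocol or analysis plan.

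A reader might infer that harm from late diagnosis will in fact be credited to surgical timing, or that days of life is the wrong exposure. The article supports neither. The bias is possible and of unknown size, and the exposure fits the stated hypothesis.

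**Conclusion.** The point holds in limited form. The main correlation and the Youden cut-off cannot separate late presentation from the wait for surgery, and the article itself names these as separate risk factors. They answer a question about total time unrepaired since birth. On their own they do not answer the question about the choice of surgical date that guidelines would govern.

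With no true effect of the wait, the chance of a significant correlation runs from about 5%, which is nominal, to about 77% at a wait SD of 6 days. It depends mainly on the share diagnosed late, the length of the delay, and the harm attached to that delay. None of these is in the article, and if few infants are diagnosed late the effect may be negligible.

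**What to change.** Keep age at surgery in days of life as the planned primary exposure. Then:

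1. Add to sections 3.1.2 and 3.1.3.4 a pre-specified model with age at admission and days from admission to surgery as separate terms, and prenatal diagnosis as a covariate.
2. Repeat the correlation and the ROC/Youden cut-off in prenatally diagnosed infants only.
3. Add the admission date to the variables in section 2.9. Total minus postoperative stay approximates the wait, but it can fail for infants transferred in or discharged before surgery.
4. State that conclusions about the choice of surgical date will be drawn only if the admission-to-surgery term supports them.

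The cost is one more recorded date, one or two extra degrees of freedom per model, and less precision in the prenatally diagnosed subset. The loss will be felt most in the smaller anatomic classes (intended n = 15 and n = 10). No new visits or assessments are needed.
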